## Methods/design

### Objectives

The main objective of the study is to estimate, by means of portable ultrasound, parameters of muscle quantity and quality of the anterior vastus of the quadriceps rectus femoris (avQRF), including muscle area, thickness, and echostructure, in older adults hospitalized in AGUs for medical reasons.

Secondary objectives are 1) to determine the prevalence of sarcopenia on admission, using the EWGSOP-2 criteria [7], 2) to determine the incidence of sarcopenia on discharge, 3) to assess the evolution of muscle mass of the avQRF between admission and discharge, 4) to evaluate changes in nutritional status, lab results, hand grip strength, gait speed, ADL, frailty, and physical performance from admission to discharge, and at 30 and 90 days for ADL and frailty, and their relationship with ultrasound muscle measurements, and 5) to analyze the relationship between ultrasound muscle measurements and other methods of muscle assessment like DXA or SARC-F. These analyses will help in the validation process of ultrasonography for muscle mass and quality assessment.

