### Sample size calculation

The main objective was to estimate quantitative parameters of avQRF, mainly the cross-sectional area values. As there were no previous normative data regarding muscle ultrasound values in hospitalized older patients, and also because our study was exploratory, we used information from previous research in Intensive Care Units to calculate the sample size. In the study from Baston et al., using Bland–Altman plots for inter-rater reliability, a measurement bias of 0.2 cm^2^ for the cross-sectional area of avQRF was described [46], allowing us to use this surrogate measure as the minimum significant value to detect real differences between measurements. Accepting an alpha risk of 0.05 and a beta risk of 0.2 in a two-sided test, 157 subjects were necessary to recognize as statistically significant a difference greater than or equal to 0.2 cm^2^ in the cross-sectional area of the avQRF. The standard deviation was assumed to be 0.8. It was anticipated a drop-out rate of 20%.

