### Statistical methods

No value imputation system was established, so the final sample size was the number of patients with values at admission and discharge for the different parameters measured. We will determine the normal distribution goodness-of-fit of the continuous variables using the Kolmogorov–Smirnov and Shapiro–Wilk tests as needed. We will calculate the mean and standard deviations in the case of normally distributed variables and the median and the interquartile range in skewed variables. 95% confidence intervals will be calculated when necessary.

Variations between hospital admission and discharge ultrasound values, DXA and anthropometric parameters, functional scales, nutritional status, cognitive status, and in general any other quantitative variable, will be calculated using paired *t*-tests, Wilcoxon tests, or Mc Nemar chi-square tests when necessary.

The prevalence of sarcopenia will be calculated as percentages. Sensitivity and specificity of ultrasound measurements to determine sarcopenia will be calculated. Kappa analysis will be used to analyze the concordance between measurements. The coefficient of variation of the ultrasound device will be calculated. Sensitivity analysis will be conducted for each participating center. All analyses will be performed with SPSS (Statistical Package for Social Sciences) statistical software, version 24.0 or later (IBM Corp. Released 2016. IBM SPSS Statistics for Windows, Version 24.0. Armonk, NY: IBM Corp).

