## Discussion

Measurement of muscle mass and function, and thereafter, identification of sarcopenia, is a challenge in hospitalized older adults [47], and multiple studies have demonstrated that it is a disease with clinical relevance in this population, associated to severe clinical outcomes [7, 9–12]. Sarcopenia is frequent in hospitalized older patients, a vulnerable population to this condition that may be present on admission or developed during hospitalization because of hospital-associated immobility [48].

In addition, sarcopenia research is difficult in complex real-world old patients, because usually they are unable to collaborate with clinical, functional, and imaging testing [47]. Measurement of grip strength, and physical function tests like gait speed, the Timed Get Up and Go test, the 5-sit-to-stand test, or the SPPB, all of them necessary to implement sarcopenia criteria [7], may be very difficult to complete in many inpatients. Moreover, DXA, BIA, CT or MRI measurements may be unaccesible to many of them. The procedure with the overall highest completion rates in a recent cohort study was ultrasound measurement of the quadriceps muscle [47]. This technique provides non-invasive, real-time assessment of muscle quantity and quality, is highly acceptable to participants, and is associated with low perceived burden when compared to other testing [49]. Ultrasound measurement of avQRF has excellent inter-rater and intra-rater variability [50, 51], and has been proposed by EWGSOP-2 for clinical assessment of sarcopenia. Different protocols for ultrasound measurements have been proposed, although final consensus is lacking, while standardization is necessary [16, 24, 51–53].

Ultrasound technology has previously demonstrated validity and reliability for muscle mass and quality assessment [13–16, 19, 20, 54–56]. In our study we used a new simple protocol that has been previously described and validated in young adults in ICU patients [24], able to quantify muscle quantity and quality. In addition, we will be able to provide associations with DXA values and physical function tests. Added value of our study will be the multicenter and longitudinal design, and the ultrasound testing acquisition by previously trained geriatricians instead of radiologists, supporting the real-life use of this technique.

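### The requirement for both an admission and a discharge value is not limited to the change analyses, so as written it also drops usable patients from the avQRF estimates and from the admission prevalence of sarcopenia

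*Protocol article*

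**What the plan says.** The rule stands at the head of Statistical methods in the protocol article: "No value imputation system was established, so the final sample size was the number of patients with values at admission and discharge". It works variable by variable, since the sentence goes on to refer to "values at admission and discharge for the different parameters measured". No analysis is exempted. Later in the section the prevalence analysis is given in one line, "The prevalence of sarcopenia will be calculated as percentages", with no denominator of its own.

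The Objectives section keeps three aims apart:

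- Main objective: "The main objective of the study is to estimate, by means of portable ultrasound, parameters of muscle quantity and quality" of the avQRF. No time point is named.
- Secondary objective 1: "to determine the prevalence of sarcopenia on admission, using the EWGSOP-2 criteria".
- Secondary objective 3: "to assess the evolution of muscle mass of the avQRF between admission and discharge".

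Of these three, only the last needs two values per patient.

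Elsewhere, the Sample size calculation allows for 20% drop-out, and Outcome measures lists death among the items assessed at discharge. The Discussion says of grip strength and physical performance tests that they "may be very difficult to complete in many inpatients".

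**The concern.** A requirement for pairs is natural for a paired test. It does not suit a descriptive estimate or a prevalence at one time point. A patient scanned and tested on admission contributes full information to both, whatever happens later. Under the rule as worded, that patient is removed if the discharge value is missing.

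Two things are at stake. The first is precision: the headline descriptive estimates would rest on fewer patients than were measured. The second is representativeness. Patients without a discharge value include those who died in hospital and those who could not be re-tested, and the document itself links sarcopenia to severe outcomes. If loss is related to muscle status, the remaining patients no longer represent those admitted. This would carry over into the comparison with published avQRF values announced under Muscle ultrasound measurements. The limitations paragraph of the Discussion does not mention this selection.

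**Working it through.** **Inputs from the protocol article.** Sample size calculation: difference 0.2 cm², SD 0.8, two-sided alpha 0.05, beta 0.2, drop-out 20%, 157 subjects. Statistical methods: the pair rule. Assumed, because the document gives no figures: the prevalence of sarcopenia, and the differences between patients with and without a discharge value.

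**1. The plan's own figure.** For a paired mean change, n = (SD × (z₀.₉₇₅ + z₀.₈₀) / difference)² = (0.8 × 2.8016 / 0.2)² = 125.6, so 126 pairs. Allowing for drop-out, 125.6 / 0.8 = 157.0. The stated 157 is reproduced. (Rounding to 126 before dividing gives 158, a rounding difference.) The plan therefore expects about 157 − 126 = 31 patients without a pair.

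**2. Precision lost for estimates that need no pair.**

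- Mean area, half-width 1.96 × 0.8 / √n: 0.125 cm² at n = 157 and 0.140 cm² at n = 126.
- Prevalence at an assumed 25%, half-width 1.96 × √(0.25 × 0.75 / n): 6.8 points at n = 157 and 7.6 points at n = 126.
- Both widen by √(157/126) = 1.12, or 12%.

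These comparisons take 157 as the upper limit. DXA was done only in selected centres and some patients may lack grip strength, so fewer may have everything needed to classify sarcopenia on admission.

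**3. Possible selection bias.** If a fraction d is dropped, the all-patient value is (1 − d) × retained + d × dropped. The error of the retained-only estimate is therefore −d × (dropped − retained). With d = 0.20:

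| Assumed prevalence, retained / dropped | All patients | Error of retained-only estimate |
|---|---|---|
| 30% / 30% | 30% | 0 points |
| 20% / 40% | 0.8 × 20 + 0.2 × 40 = 24% | −4 points |
| 40% / 80% | 0.8 × 40 + 0.2 × 80 = 48% | −8 points |

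For mean area, if dropped patients average 0.2, 0.4 or 0.8 cm² less (assumed), the retained mean is too high by 0.2 × 0.2 = 0.04, 0.2 × 0.4 = 0.08 or 0.2 × 0.8 = 0.16 cm².

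**4. What is not affected.** The paired change analysis needs pairs in any case, and its sample size calculation is unchanged.

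**The case against.** The strongest reply is that the rule was meant only for the paired comparisons described in the next paragraph of Statistical methods. Table 1 schedules MNA-SF and laboratory results at baseline only, and SARC-F only for the pre-hospitalization period. Read literally, the rule would leave no patients for these variables, although secondary objectives 4 and 5 use them. The phrase about final sample size also fits a calculation built on 126 pairs. This narrower reading is plausible. But the text does not state the limit and gives no other denominator for prevalence, so the sentence needs correcting under either reading.

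Other parts of the reply stand and limit the point:

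- A reader might infer that the estimates are shown to be biased toward the fitter. The document gives no reasons for missing discharge values and does not break down the 20%. Early discharge of fitter patients could offset the effect. The remark on difficult tests concerns grip and performance testing in general, and the same section reports that quadriceps ultrasound had the highest completion rates in a cohort study. The exclusion criteria also remove terminal patients and those judged unable to complete the procedures.
- A reader might call the main objective admission-only. No time point is named, and the Background speaks of longitudinal estimation. What can be said is that the objective does not need a discharge value.
- A reader might conclude that the paired change analysis is valid only if values are missing completely at random. That is too strict: the mean change from complete pairs is unbiased whenever missingness is unrelated to the change itself, even if it depends on the admission level.

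The study is also exploratory, and the loss of precision is modest.

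**Conclusion.** The point holds as a defect of wording with consequences for two descriptive results. As written, the pair rule removes patients with usable admission data from the avQRF estimates and from the admission prevalence, about 31 of 157 at the planned loss. Because the rule acts on each parameter separately, the actual loss will differ between variables.

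The cost in precision follows from the planned 20% loss and, for area, the plan's SD; for prevalence it also uses the assumed 25%. It is small: intervals about 12% wider. The bias is a risk and not a demonstrated error. Its size depends wholly on assumed differences and ranges from none to 8 prevalence points over the scenarios shown. Selection toward fitter patients is the likelier direction, since deaths and patients not re-tested are dropped, but the document does not establish it.

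**What to change.** Amend the opening sentence of Statistical methods so that:

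1. The requirement for both values applies only to the admission-to-discharge change analyses.
2. avQRF admission values are summarised in all patients with that measurement, and the admission prevalence in all patients with the admission measurements needed for classification, each with its own denominator.
3. In-hospital deaths, reasons for missing discharge values where these were recorded, and the admission characteristics of patients with and without discharge values are reported next to the change results.

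The analyses are still described in the future tense, and none of this needs new data collection. The cost is that denominators will differ between analyses and must be shown, with slightly more reporting.

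Replacing the paired tests by a mixed model is not needed to settle this point. It would also imply discharge values for patients who died in hospital, which is open to debate.

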## Discussion

Measurement of muscle mass and function, and thereafter, identification of sarcopenia, is a challenge in hospitalized older adults [47], and multiple studies have demonstrated that it is a disease with clinical relevance in this population, associated to severe clinical outcomes [7, 9–12]. Sarcopenia is frequent in hospitalized older patients, a vulnerable population to this condition that may be present on admission or developed during hospitalization because of hospital-associated immobility [48].

In addition, sarcopenia research is difficult in complex real-world old patients, because usually they are unable to collaborate with clinical, functional, and imaging testing [47]. Measurement of grip strength, and physical function tests like gait speed, the Timed Get Up and Go test, the 5-sit-to-stand test, or the SPPB, all of them necessary to implement sarcopenia criteria [7], may be very difficult to complete in many inpatients. Moreover, DXA, BIA, CT or MRI measurements may be unaccesible to many of them. The procedure with the overall highest completion rates in a recent cohort study was ultrasound measurement of the quadriceps muscle [47]. This technique provides non-invasive, real-time assessment of muscle quantity and quality, is highly acceptable to participants, and is associated with low perceived burden when compared to other testing [49]. Ultrasound measurement of avQRF has excellent inter-rater and intra-rater variability [50, 51], and has been proposed by EWGSOP-2 for clinical assessment of sarcopenia. Different protocols for ultrasound measurements have been proposed, although final consensus is lacking, while standardization is necessary [16, 24, 51–53].

Ultrasound technology has previously demonstrated validity and reliability for muscle mass and quality assessment [13–16, 19, 20, 54–56]. In our study we used a new simple protocol that has been previously described and validated in young adults in ICU patients [24], able to quantify muscle quantity and quality. In addition, we will be able to provide associations with DXA values and physical function tests. Added value of our study will be the multicenter and longitudinal design, and the ultrasound testing acquisition by previously trained geriatricians instead of radiologists, supporting the real-life use of this technique.

The main limitations of the study is the unknown feasibility of the selected protocol for its use in hospitalized older adults, the possibility of a low inter-rater reliability between geriatricians albeit the training, or the heterogeneity of older adults regarding pathologies, functional status or medicines, because our study is non-interventional, only exploratory. Another limitation is that we will not be able to differentiate between sarcopenia and cachexia, although this is not the objective of the study. Cachexia is a common manifestation of several serious illnesses, such as chronic heart failure or cancer, it is associated with chronic inflammation, and in many cases it is related with hospitalization. However, sarcopenia and cachexia can overlap in the same older patient, and differential diagnosis might be difficult in clinical practice, as there is no clear demarcation line between them, or screening and diagnostic tools to clearly identify them [57, 58].

However, we think that the results obtained will be of great interest to the scientific geriatric community to assess the utility of ultrasound measurements for the detection and follow-up of sarcopenia in hospitalized older adults. Future research will need to validate the measurement methodology, describe cut-off points, and identify future strategies for management.

## Abbreviations

ICD-10-CM: International Classification of Disease, Tenth Revision, Clinical Modification
EWGSOP: European Working Group on Sarcopenia in Older People
ADL: Activities of Daily Living
BIA: Bioelectrical Impedance Analysis
MRI: Magnetic Resonance Imaging
CT: Computed Tomography
DXA: Dual energy X-ray Absorptiometry
AGU: Acute Geriatric Units
avQRF: Anterior vastus of the Quadriceps Rectus Femoris
GDS: Global Deterioration Scale from Reisberg
BMI: Body Mass Index
FAC: Holden Functional Ambulation Classification
SPPB: Short Physical Performance Battery (SPPB)
Kg: Kilograms
EAT-10: Eating Assessment Tool- 10 questionnaire
MNA-SF: Mini Nutritional Assessment Tool – Short Form
LDL: Low-Density Lipoproteins
HDL: High-Density Lipoproteins
ESR: Erythrocyte sedimentation rate
CRP: C-reactive protein
aLM: Appendicular lean mass
mm: Millimeters
QRF: Quadriceps rectus femoris
cm: Centimeters
BMI: Body mass index
S: Sensitivity
E: Specifity
IRB: Institutional Review Board
eCRF: Electronic Case Report Form
REDCap: Research Electronic Data Capture
SPSS: Statistical Package for Social Sciences
